## Methods/design

### Participants

This is a part of a larger project which is designed to comprehensively investigate the efficacy of different tDCS protocols at different sites of brain for treatment of intractable chronic tinnitus. In this double blinded placebo controlled randomized trial will be conducted on intractable tinnitus patients (n=90) who will be randomly divided into three groups of anodal (anode/cathode on left/right AC), cathodal (cathode/anode on left/right AC, and sham (anode/cathode on left/right AC) tDCS. In the sham treatment, after 30 sec the device will be turned off without informing the patients. The experimental procedures of the study including tDCS interventions and the evaluations of the outcomes will be performed in the Bioelectromagnetic Clinic in Ahvaz Imam Hospital, Ahvaz, Iran. Patients with intractable chronic tinnitus (> 2 years) will be enrolled in this study. This is a single-center, non-stratified, with balanced randomization [1:1:1], double-blind, placebo-controlled, parallel-group study conducted in Bioelectromagnetic Clinic, Imam Khomeini Hospital, Ahvaz, Iran. Allocation concealment will be performed by random allocation cards using computer-generated random numbers. The patients will be randomly assigned into three groups of cathodal, anodal, or placebo tDCS.

### Ethics approval and consent to participate

All of the experimental procedures of this study were approved by the local ethics committee of Ahvaz Jundishapur University of Medical Sciences, Ahvaz, Iran (registration code: IR.AJUMS.REC.1394.639) which were in complete accordance with the ethical standards and regulations of human studies of the Helsinki declaration (2014)
^25^. After enrolment and before the start of the study, researcher will clearly explain the experimental procedures, the objectives, possible benefits, and side effects of the study to the patients and then all participants will fill and sign a written consent form for contribution in the study. The study was registered as a clinical trial in the Iranian registry of clinical trials (
IRCT2016110124635N6).

### Inclusion and exclusion criteria

The patients should meet specific criteria for inclusion in this project. The primary criteria will be evaluated during the neurological and otolaryngological examinations by experienced specialists. The patients will be selected among the tinnitus patients referred to the Tinnitus Clinic in the Khuzestan Cochlear Implant Center, Ahvaz, Iran. After the start of the study and anytime during the study, patients have the right to leave the study. In case of any significant adverse effects (AEs), the procedures for the respective patients will be terminated.

**Inclusion criteria**

• Idiopathic chronic and medication-resistant tinnitus (more than 2 years)• Age range of 18 to 70 years old• No use of medications at the time of intervention

**Exclusion criteria**

• History of epileptic seizures, brain trauma• Severe psychotic and psychiatric disorders• Concurrent severe vertigo• Meniere's disease• Severe organic comorbidity• Using pacemaker or defibrillator• Present pregnancy, neurologic disorders such as brain tumors,• Concurrent treatment for mental disorders.

All prospective subjects will undergo complete audiometric and neurologic examinations by experienced specialists. The experimental procedures of the study including tDCS interventions and the evaluations of the outcomes will be performed in the Bioelectromagnetic Clinic in Ahvaz Imam Hospital, Ahvaz, Iran.

### Study protocol

This study is a double-blind randomized controlled clinical trial design and patients will be randomly assigned into three groups of anodal and cathodal tDCS and sham tDCS. The random allocation will be performed based on balanced randomization [1:1:1] where the allocation concealment will be applied by random allocation cards using computer-generated random numbers. The three groups will be matched for age, gender, ethnicity, and audiometric main characteristics. To reduce the procedure and subjective bias, the patients, the researchers who will evaluate the outcomes, and the researchers who perform data analyses will be blinded on the type of protocol. In addition, the blinding quality of the study will be assessed after completion of the intervention.

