## Statistical assessments

All statistical tests will be performed using
SPSS (V20.0, IBM Corporation, New York, USA). To determine whether the anodal, cathodal, and sham tDCS groups are well-matched in terms of age, sex, quality of tinnitus, tinnitus laterality, THI score, and duration and class of hearing loss, these dependent variables will be compared between the three groups using independent samples t-tests.

For nominal data like gender and class of hearing loss, Chi-square tests will be conducted across groups. Independent sample t-tests were also used to determine if individual baseline measures differed between groups (THI, tinnitus loudness, and distress). Prior to conducting
*t*-tests, Levene’s test for equality of variances was used. In no instance was Levene’s test violated; thus, equality of variances was assumed. The number of female and male participants and the quality of tinnitus symptoms, across each group will be compared using Pearson Chi-square tests. Mixed repeated-measure ANOVAs with the within‐subject factor time and the between‐subject factor stimulation were performed for evaluating changes in THI, tinnitus loudness, tinnitus distress, BDI and BAI scores. For the ANOVAs, sphericity was tested with the Mauchly’s test, and in the event of a violation of Mauchly’s test, the Greenhouse-Geisser correction was applied. In case of significant effects, follow-up post-hoc t-tests were carried out using LSD adjustments for multiple comparisons to examine if tDCS caused a significant difference relative to sham or baseline. An analysis of covariance will be performed with Time as within-subject factor, Stimulation as between-subject factor, and gender, laterality of tinnitus, duration of tinnitus as covariates. In addition, we will calculate Pearson’s correlations between change of THI and tinnitus loudness and distress values from pre- to post-stimulation.

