## Trial status

To date, the enrollment of the patients has been performed and the allocation will be performed in the near future. The study is supposed to be started in end of January and finished in August 2018.

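### The protocol promises three groups matched on four characteristics, but the non-stratified 1:1:1 allocation it describes cannot guarantee this and no covariate-based random method is named

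*Protocol article*

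**What the plan says.** Four places in the protocol article bear on this.

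- **Study protocol:** "The three groups will be matched for age, gender, ethnicity, and audiometric main characteristics". The sentence before it gives the method as "balanced randomization [1:1:1] where the allocation concealment will be applied by random allocation cards using computer-generated random numbers".
- **Participants:** "This is a single-center, non-stratified, with balanced randomization [1:1:1], double-blind, placebo-controlled, parallel-group study". The same section repeats the allocation cards and random numbers.
- **Statistical assessments:** baseline comparisons are planned "To determine whether the anodal, cathodal, and sham tDCS groups are well-matched in terms of age, sex, quality of tinnitus, tinnitus laterality", and on further variables. The covariates of the planned analysis of covariance are "gender, laterality of tinnitus, duration of tinnitus as covariates".
- **Trial status:** "the enrollment of the patients has been performed and the allocation will be performed in the near future".

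No section mentions strata, minimisation, matched sets or constrained randomisation.

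**The concern.** Matching is a property of the allocation method. If groups are to be matched on age, gender, ethnicity and audiometry, some rule must use those characteristics when patients are allocated. The only scheme described uses none of them and is labelled non-stratified. The two statements do not fit together.

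Two things are at stake. First, the trial report may describe the groups as matched when they are only randomised, and with 25 to 30 patients per arm visible differences can easily arise. Second, staff who are told that the groups will be matched, but are given no random method for it, have an unclear instruction at a sensitive time. Enrolment is complete, and demographic and audiological assessment belongs to the enrolment stage in Table 2, so the patients' characteristics are known before anyone is allocated.

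**Working it through.** **Comparing the statements**

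| Question | Study protocol | Participants | Statistical assessments |
|---|---|---|---|
| Are covariates used in allocation? | Matching promised on four factors, no method given | Non-stratified | Not addressed |
| Method | 1:1:1, cards, computer-generated numbers | The same | Not addressed |
| Status of matching | Will be achieved | Not addressed | To be checked after allocation |

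The list checked after allocation is not the list promised. Ethnicity is absent, and THI, tinnitus quality, laterality and duration are added. Of the four promised factors, only gender is among the covariates.

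**How large chance imbalance can be under the stated scheme**

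The protocol gives no figure for this, so there is nothing to reproduce.

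Inputs:
- Patients per arm, n: 25 (Sample size calculation) or 90/3 = 30 (Participants). The article gives both totals; that is a separate matter, so both are carried through.
- Prevalence p of a yes/no factor: not stated. Assumed range 10% to 50%; 50% gives the largest imbalance.

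Formula: let X and Y be the numbers with the factor in one active arm and in sham, independent Binomial(n, p). The probability is the sum of P(X = i) × P(Y = j) over all i, j with |i − j| ≥ 0.20n. The cut-off is 0.20 × 25 = 5 patients or 0.20 × 30 = 6 patients.

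| Prevalence | 25 per arm | 30 per arm |
|---|---|---|
| 50% | 0.203 | 0.155 |
| 30% | 0.164 | 0.120 |
| 20% | 0.110 | 0.075 |
| 10% | 0.034 | 0.018 |

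These are for one active arm against sham on one factor. For either active arm on at least one of two independent factors, simulation gives about 56% and 46% at 50% prevalence, 48% and 37% at 30%, and 12% and 7% at 10%.

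For one continuous factor such as age, simulation of three equal arms puts the largest gap between arm means at 0.5 SD or more in about 18% (25 per arm) or 13% (30 per arm) of randomisations. For at least one of four independent continuous factors the probability is 1 − (1 − 0.18)^4 ≈ 0.55, or 1 − (1 − 0.129)^4 ≈ 0.42.

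The scheme therefore gives balance on average but does not guarantee it in this trial.

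**The case against.** A reader might go further and infer that the promise can be kept only by moving patients between groups by hand, so that either the statement is false or randomisation is broken. The protocol does not support this. No section describes swapping or reassigning patients, and both descriptions of allocation specify computer-generated random numbers. Nor is hand adjustment the only route. Minimisation with a random element and covariate-constrained randomisation pursue balance validly, as does randomising within matched sets, although the last sits less well with a non-stratified design. Having all patients enrolled before allocation makes these methods feasible.

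The milder reading also has support. The Statistical assessments section treats being well-matched as something to check, so the word may be loose language for expected balance. Even so, the sentence promises more than the scheme can deliver.

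Three further points limit the consequence:
- Chance imbalance after proper randomisation does not invalidate the tests; the type I error rate already allows for it.
- The protocol gives no prognostic strength for gender or hearing, so the probabilities above show that arms can differ, not that the result would be distorted.
- Audiometry is not ignored in the analysis: the Hearing assessment section plans to study its interactions with the outcomes. That is not the same as adjusting the treatment comparison for it.

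How the random list is generated is detail an article may leave to the full protocol. That would excuse a missing detail, but not two stated features that disagree.

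**Conclusion.** The inconsistency is real and should be corrected before allocation. The protocol promises matching on four factors, describes only a non-stratified scheme that balances them in expectation, and names no covariate-based random method. Hand adjustment is a risk left open by the wording, not a documented plan.

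The size depends on unstated prevalences. A gap of 20 points or more between a given active arm and sham on one binary factor has a probability of 20% (25 per arm) or 16% (30 per arm) at 50% prevalence, falling to 3% or 2% at 10%. The consequence is some loss of precision, as far as the factors predict THI, and a claim of matched groups that could be untrue. The loss of precision cannot be quantified from the protocol.

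**What to change.** 1. Delete the sentence saying the groups will be matched.
2. Before allocation starts, choose one of two routes:
   - keep simple 1:1:1 randomisation and claim only expected balance; or
   - name a random balancing method, for example permuted blocks stratified by gender and hearing class, or minimisation with a random element, and correct the non-stratified label under Participants. If hearing class is used, state how the two ears are combined.
3. State that no patient is exchanged between groups after allocation.
4. In either case, analyse post-treatment THI adjusted for baseline THI, any stratification factors, age and hearing level. This replaces the time-by-group ANOVA as the primary model and covers promised factors that the allocation may leave unbalanced.

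The cost is small: a slightly more complex list if the second route is taken, and a few model terms using data already collected or scheduled. The choice of allocation method is open only until the first patient is allocated; after that, only the adjustment in the analysis remains.

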### Transcranial direct current stimulation protocol

The direct current will be applied through a saline-soaked pair of surface electrodes (35 cm
^2^) and delivered by a tDCS device which is a specially developed, battery-driven, constant current stimulator with a maximum output of 2 mA. The tDCS device used in this study will be an OASIS Pro
^TM^ device by Mind Alive Inc (Edmonton, Alberta, Canada). Anodal and cathodal tDCS groups will consist of daily 20-min sessions of 2 mA current for five consecutive days per week and for 2 consecutive weeks (10 sessions in total). In anodal tDCS, the anode and cathode will be respectively centered over left AC (halfway T3 - F7) and right AC (halfway T4 - F8). In the cathodal tDCS the electrodes position will be reversed where cathode and anode will be respectively centered over left AC (halfway T3-F7) and right AC (halfway T4-F8). The site of electrodes will be selected according to the
International 10-20 electroencephalography system. In the sham tDCS group, the electrode montage will be the same as the anodal tDCS, but the device will be turned off after 30 s without the knowledge of the participant. These parameters for sham stimulation were chosen based on previous reported findings where the perceived sensations of stimulation on the skin, such as tingling, usually disappear in the first 30 s of active tDCS
^23,
26^ (
Table 1).

**Table 1. T1:** Setting for anodal, cathodal, and sham Transcranial Direct Current Stimulation (tDCS).

	Anodal tDCS	Cathodal tDCS	Sham tDCS
Current density	57.1 µA/cm ^2^	57.1 µA/cm ^2^	57.1 µA/cm ^2^
Electrode montage	Anode left (halfway T3 - F7) and cathode right AC (halfway T4 - F8)	Cathode left (halfway T3 - F7) and anode right AC (halfway T4 - F8)	Anode left (halfway T3 - F7) and cathode right AC (halfway T4 - F8)
Duration	20 min	20 min	20 min ^*^

Note: * 30 seconds after the start of the stimulation the device will be turned off without the knowledge of patient.

### Adverse effects and tolerability

The previous studies on the safety and tolerability of tDCS have shown that the 2 mA current applied in 20 minutes are associated with no serious AEs
^24,
26^. The common reported AEs are itching or tingling sensation, mild headache or fatigue and local burns at the site of stimulation. However, most of the AEs and tolerability assessments have been performed on the tDCS were for single session ranging 20–30 minutes and current of 1 to 2 mA. In our study, we will use repeated sessions of tDCS (2 mA current for 20 minute, total 10 sessions, daily one session, five consecutive days per week and 2 consecutive weeks), thus the reported AEs in the previous studies may be intensified. Therefore, we will assess the AEs using a customized questionnaire (
Supplementary File 1). The questionnaire will be performed during and after each tDCS session to record all the perceived AEs from the patients in all three tDCS groups.

## Outcome assessments

### Baseline evaluations

There will be different evaluations before the intervention. After enrollment, the patients will undergo complete audiometric and neurological assessments by expert specialties. The tinnitus severity for each patient will be determined through asking the patient and confirming the class by an expert otolaryngologist as buzzing, cicadas, high pitch whistling, hissing, humming, ringing, pulsating, thumping, and ticking. The tinnitus laterality and duration will be also determined.

### Hearing assessment

Hearing assessments will be performed in an acoustically isolated chamber (ISO 8253–1:2010). Pure-tone audiometry will be performed using AC 40 dual channel Audiometer (Intracoustics Co., Denmark). The hearing thresholds will be recorded over the frequency ranges of 250 to 8000 Hz for air conduction and 500 to 4000 Hz for bone conduction pathways, using the modified Hughson–Westlake Method as per recommended by ANSI 1997
^27^. Pure-tone audiometry is considered normal when the hearing thresholds at all frequencies are below 20 decibels hearing level (dBHL). Hearing loss will be classified according to the type and degree
^28^. The class of hearing loss in both ears will be assessed as normal hearing threshold (<20 dB), mild hearing loss (20 – 40 dB), moderate hearing loss (41 – 70 dB), severe hearing loss (70 – 90 db), and profound hearing loss (> 90 db). The hearing class is determined as the average of threshold in 250 Hz, 1000, 2000, and 4000 Hz. The possible interactions of the aforementioned variables and the amount of each primary or secondary outcome will be studied.

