21^. The main hypothesis for therapeutic application of tDCS in tinnitus is disturbing ongoing abnormal neural activities responsible for tinnitus. According to this approach, the areas involved in the pathophysiology of tinnitus are targeted by tDCS. The other hypothesis of eliciting therapeutic outcomes from tDCS is inducing plastic changes to alter the maladaptive plasticity of the involved regions. The important point for treatment of tinnitus is that there is a large network consisting of different auditory and non-auditory regions with overlapping functions
^22–
24^.

Most of the studies performed to date, have focused on the effects of single tDCS session on tinnitus symptoms, with short term follow ups ranging some hours to some days. To our knowledge, there is no published study investigating the effect of repeated sessions of tDCS over the auditory cortex (AC) on tinnitus symptoms as well as the AEs of and tolerability to the tDCS with one month follow up. This study aims to investigate the effects of repeated sessions of tDCS on tinnitus symptoms with one month follow-up. Our main hypothesis is that repeated sessions will lead to aggregative therapeutic effects on tinnitus. In addition, we want to evaluate possible association between treatment response, and patient's and tinnitus specific characteristics including gender, THI basal score, laterality, tinnitus quality, duration, hearing loss class, etc.

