### Outcomes assessments

The primary and secondary outcomes will be measured in two main time points: pre- and post-intervention. The pre-intervention assessments of the outcomes will be performed at the first day of the intervention before tDCS stimulation (T
_1_). There will be four time points of post-intervention assessments as T
_2_, T
_3_, T
_4_, and T
_5_ corresponding to the immediately after last session, one hour, one week, and one month after last tDCS session.
Table 2 represents the SPIRIT schematic protocol of the study and timing of the assessments.

**Table 2. T2:** Standard Protocol Items: Recommendations for Interventional Trials of this study.

	Enrolment	Allocation	Pre- intervention	Intervention	Post- intervention			
TIME POINT	*-T _1_*	T _0_	*T _1_*		*T _2_*	*T _3_*	*T _4_*	*T _5_*
ENROLMENT:								
Eligibility screen	X							
Informed consent	X							
*Demographic* *information*	X							
Allocation		X						
INTERVENTIONS:								
*real (anodal and* *cathodal) tDCS*								
*Sham tDCS*								
ASSESSMENTS:								
*Neurological* *and audiological* *assessments*	X							
*Hearing loss* *assessment*	X							
*Primary outcome:* *THI*			X		X			X
*Secondary outcomes:* *loudness*			X		X	X	X	X
*Distress*			X		X	X	X	X
*AEs and Tolerability*					X			

Note: THI: tinnitus handicap inventory; AEs: adverse effects, -T
_1_: one month before intervention, T
_0_: one day before intervention, T
_1_: 5 min before intervention, T
_2_: immediately after last session, T
_3_: at hour after last session, T
_4_: one week, and T
_5_: at month after last tDCS session. Real tDCS refers to anodal and cathodal tDCS groups.

***Primary outcome***. Tinnitus handicap inventory (THI) score will be the primary outcome. The THI is a 25-item questionnaire and commonly used as self-reporting inventory for disabling level of tinnitus. The THI items are grouped into three subscales: Functional (11 items), emotional (9 items), and catastrophic (5 items) subscales. Each item is three point Likert type scale with three alternative assessments: yes (4 points), sometimes (2 points), and no (0 point). The questionnaire yields scores for each subscale and a total score that ranges 0 to 100, where higher score means more severe tinnitus or a greater handicap

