***Secondary outcomes***

**Tinnitus loudness and distress**. The tinnitus loudness and distress will be assessed using a numeral 0–10 visual analogue scale rating scale before intervention, and immediately, one hour, one week, and one month after last tDCS session. For tinnitus loudness and distress a 10 percent or 2 point reduction of 0–10 scale will be considered as treatment response
^31,
32^.

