Finally, we will examine the number of responders versus non-responders under each treatment condition (anodal, cathodal, and sham). This will be accomplished by calculating change scores between the pre-treatment and post-treatment THI values (Pre-treatment – Post-treatment). Responders will be considered individuals who showed reductions in THI score of equal or more than 20 points in the THI score (Pre-treatment THI – Post-treatment THI ≥ 20). For tinnitus loudness and distress a 10 percent or 2-point reduction of 0–10 scale is considered as treatment response. Pearson’s chi-square tests will be used to evaluate whether there are differences in the proportion of responders versus non-responders under each condition. For all statistical tests the P-value < 0.05 is defined as statistically significant level.

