## Discussion

Recent studies have shown beneficial effects of tDCS in improving cognitive functions in healthy individuals
^7^ and also symptoms of different neuropsychiatric disorders such as depression
^8^, obsessive compulsive disorder
^9^, auditory-verbal hallucinations
^10^, and chronic pain
^11^. The therapeutic effects of tDCS in tinnitus have been reported by several studies; however, the findings are heterogeneous and controversial. In addition, most of the conducted studies have focused on single session tDCS, with short follow-up periods ranging some hours, to a few days
^13,
16,
33^. The present study aims to investigate the therapeutic efficacies of repeated sessions of bilateral tDCS (anodal/cathodal over the left/right AC) on tinnitus symptoms, its loudness, and distress in patients with intractable chronic tinnitus. The main advantage of this study is that it is a double blinded which will remove the placebo effects of the tDCS. The other main advantage of this study is the one month follow-up which is relatively long period, compared to the previous studies. Moreover, we aim to evaluate the possible interactions between the disease specific features and treatment response to develop a more specific and disease oriented tDCS protocol. To our knowledge this will be the first study of repeated sessions of tDCS with one month follow-up. Considering the repeated sessions of tDCS in this study, we will investigate the AEs of and tolerability of the patients in this study.

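### Several patient and tinnitus features are to be related to response on three outcomes at P<0.05, uncorrected and not labelled exploratory, with the aim of shaping a tDCS protocol; the chance of a false modifier reaches about even on the broadest reading

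*Protocol article*

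**What the plan says.** **Features.** The Background of the protocol article wants to relate treatment response to patient and tinnitus characteristics, "including gender, THI basal score, laterality, tinnitus quality, duration, hearing loss class, etc". That is six features and an open end. The Abstract names three (hearing loss, laterality, type of tinnitus). Baseline evaluations and Hearing assessment together describe four (type, laterality, duration, hearing loss). Statistical assessments enters three as covariates (gender, laterality, duration) and states no feature-by-stimulation term.

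**Outcomes.** Hearing assessment closes with: "The possible interactions of the aforementioned variables and the amount of each primary or secondary outcome will be studied". There are three such outcomes: "Tinnitus handicap inventory (THI) score will be the primary outcome", and, as secondary outcomes, "The tinnitus loudness and distress will be assessed using a numeral 0–10 visual analogue scale rating scale".

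**Threshold.** "For all statistical tests the P-value < 0.05 is defined as statistically significant level". The only multiplicity wording concerns the ANOVA: "follow-up post-hoc t-tests were carried out using LSD adjustments for multiple comparisons".

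**Purpose.** The Discussion says that the investigators aim "to evaluate the possible interactions between the disease specific features and treatment response to develop a more specific and disease oriented tDCS protocol".

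**The concern.** Testing several features on several outcomes, each at 0.05, forms a family of tests whose chance of at least one false positive is well above 0.05. That is tolerable when the family is declared exploratory. Here the article applies one threshold to all tests, makes no such declaration, and gives the analysis a developmental purpose. The LSD procedure does not help: it leaves each comparison at 0.05 and is attached only to the ANOVA post-hoc tests.

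At stake is what the trial may conclude about who responds. A modifier found by chance could be reported as significant under the article's own rule and carried into a tailored protocol. The open list also allows features to be added after the data are seen. The main comparison of active with sham stimulation is not affected.

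**Working it through.** **The plan's own figure.** The article states no error rate for the modifier analyses, so there is none to reproduce. The nearest stated figure is the sample size of 22 (read as per group) at 85% power and 95% confidence. Equation 1 cannot be recomputed because the mean difference and SDs are not given. With equal SDs it can be back-solved:

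d = (1.960 + 1.036) × √(2/22) = 0.90 SD.

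**Inputs for the family**
- Per-test level 0.05 (Statistical assessments), taken as two-sided because Equation 1 uses the 1−α/2 quantile.
- Features: 6 (Background), 4 (Baseline evaluations with Hearing assessment), 3 (Abstract, or Statistical assessments).
- Outcomes: 3 (THI, loudness, distress), or THI alone.
- One test per feature and outcome, and no true modifier.
- Outcome correlation 0.3–0.8 and feature correlation 0–0.5. Both are assumptions; the article gives neither.

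**Independent tests, as an upper reference:** 1 − 0.95^k
- k = 6 × 3 = 18: 0.60, with 18 × 0.05 = 0.9 false positives expected
- k = 4 × 3 = 12: 0.46
- k = 3 × 3 = 9: 0.37
- k = 6 (THI only): 0.26

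**Correlated tests.** Two-sided normal tests were simulated with the assumed correlations; a test counts as positive if |z| > 1.96.

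| Family | Lowest (features 0.5, outcomes 0.8) | Highest (features 0, outcomes 0.3) |
|---|---|---|
| 6 features × 3 outcomes | 0.37 | 0.59 |
| 4 features × 3 outcomes | 0.29 | 0.44 |
| 3 features × 3 outcomes | 0.23 | 0.36 |
| 6 features × THI only | 0.21 (features 0.5) | 0.26–0.27 (features 0) |

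At outcome correlation 0.5 with independent features, the 6 × 3 figure is 0.55. One more feature admitted through the open list (7 × 3) gives 0.40–0.64. Testing time points or the two active arms separately would raise all of these.

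**How much one significant modifier would tell.** Take a 50/50 binary feature, one active arm against sham, and an interaction as large as the back-solved 0.90 SD. The standard error is √(4/(n/2)) in SD units.
- n = 22: 0.90/0.603 = 1.50; power = Φ(1.50 − 1.96) = 0.32
- n = 25: 0.90/0.566 = 1.60; power = 0.36
- n = 30: 0.90/0.516 = 1.75; power = 0.42

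All three sizes are shown because Sample size calculation gives 22 raised to 25 per group, while the 90 patients elsewhere imply 30. Low power with an inflated false-positive rate makes an isolated P<0.05 modifier weak evidence.

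**The case against.** **The grid of tests is not written down.** A reader might infer at least 18 modifier tests. The article does not support that as a minimum. It joins the Background's list, which speaks of association with treatment response, to the Hearing assessment sentence, whose back-reference reaches at most hearing loss, tinnitus type, laterality and duration. Statistical assessments plans no explicit interaction test. This stands, so the narrower readings are given beside the broad one. They lower the figure without removing the problem: three features on three outcomes still give 0.23–0.36.

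**A false modifier is not shown to be likely.** A reader might infer that it is. Even six features on three outcomes give 0.37–0.59, which is around even, and the other readings fall below that. This also stands.

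**The wording is subordinate.** The Background sets its main hypothesis apart, and the modifier aims are phrased as possible associations or interactions. No rule says that one P<0.05 would fix a protocol, so it would be inference to say that the trial will adopt one on that basis. But the soft wording concerns whether effects exist; it does not change the threshold or the declared purpose.

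**An article may leave this to the analysis plan.** Ranking and labelling of secondary analyses often sit there, and their absence alone would be no finding. The point rests on what the article does fix: one threshold for all tests, an open list, all outcomes and a developmental aim. A later plan that applied a stricter threshold would contradict that rule as written.

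**Conclusion.** The point holds in a limited form. If the article's threshold is applied to the modifier analyses it announces, the chance of at least one false modifier when none exists is about 0.37–0.59 for six features on three outcomes, 0.29–0.44 for four, 0.23–0.36 for three, and 0.21–0.27 for six on THI alone. These figures rest on one test per feature and outcome and on the assumed correlations. The number of tests is itself not fixed, because the feature lists differ between sections and one is open. It should be corrected because it governs what may be claimed about responders; it does not threaten the primary comparison.

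**What to change.** 1. Give one closed feature list, identical in the Abstract, Background, Hearing assessment and Statistical assessments, with no open end.
2. State in Statistical assessments that the modifier analyses are exploratory and exempt from the P<0.05 rule.
3. Report feature-by-stimulation interaction estimates with 95% confidence intervals. The covariate terms now named do not by themselves provide these.
4. Reword the Discussion aim so that the analysis generates hypotheses for a disease-oriented protocol.

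Holm across the listed features on THI is an option only if a confirmatory modifier claim is wanted. With six features its first step needs P < 0.05/6 = 0.0083. At 25 per group, power for the interaction above would then be about Φ(1.60 − 2.64) = 0.15. It would also leave loudness and distress outside the confirmatory claim. That trade-off is for the investigators to weigh.

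The recommended change needs no extra patients or measurements. Its cost is that a single P<0.05 modifier can no longer be presented as established. The Trial status section puts allocation still ahead, so on that account the change can be made before outcome data exist.
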